##### Immunological markers in serum

Blood samples will be collected from all participants twice during the study: one sample at baseline and one sample post treatment. Plasma will be separated by centrifuge within 30 minutes, frozen at −80°C and stored until analyses in batches. The serum concentration of the following regulating inflammatory cytokines will be assessed: IL-1β, IL-2, IL-4, IL-5, IL-6, IL-8, IL-10, IL-12, IL-13, IL-17, IL-21, IL-22, IL-23, TNFα, IFNγ.

### Sample size

The sample size calculation for the primary outcome measure, the QEESI Life Impact Scale, is based on a two-sample *t* test. A recent study among Danish MCS patients found a mean value of 61.5 with a standard deviation of 24.3 on the Life Impact Scale [46]. In this study, the intervention is expected to induce a 40% decrease on this scale. We thus expect the mean QEESI score in the intervention group to decrease to 36.9 and the mean QEESI score in the control group to remain unchanged. Since we do not know the standard deviation of the change score we base our sample size calculation on the assumption that the standard deviation of the change score is 24.3. Under these assumptions and with a two-sided significance level set at 0.05, the study will require 17 participants in each group to be able to reject the null hypothesis with a power of 0.80. Expected dropouts are estimated at three participants in each group, which means that the total number of participants needed is 40.

### Statistical analyses

Statistical analyses will be conducted using SPSS (SPSS Inc, Chicago, IL, USA) and SAS (SAS Institute Inc, NC, USA). Data will be anonymized and analyzed by a statistician blinded to the participants’ group affiliation; that is, intervention group or control group. The statistician will remain fully masked during planning and conduction of the statistical analyses. Descriptive statistics for the two groups will be generated. Intention-to-treat analyses with a two-sided significance level at 0.05 will be conducted using the mixed-model repeated-measures method for continuous measures. This model ensures that data values which are missing at random will not create bias. Sensitivity analyses will be used to assess the possible impact of nonrandomly missing values. Prevention of missing values will be attempted by reminding (email and/or telephone) the participants to fill in the questionnaires. Since PEMF therapy is a new approach to treating MCS, per-protocol analyses will be carried out additionally to evaluate a possible treatment effect, if Re5 therapy is applied as specified; that is, compliance ≥80%. The final analyses will be adjusted for baseline levels to improve power. According to the sample size calculation, the two-sample *t* test will have sufficient power to detect a treatment effect, but a mixed model, which utilizes all available data, is likely to be more powerful. The criteria of success in the study are significantly positive changes in the intervention group compared with the control group regarding the primary and secondary outcomes.

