### Hypotheses

The primary hypothesis is that PEMF therapy can significantly reduce the impact of MCS on everyday life in the intervention group compared with the control group. The secondary hypotheses are that PEMF therapy can significantly decrease: general symptoms (that is, symptoms that are commonly experienced by MCS patients); exposure-related symptoms (that is, symptoms that are elicited by exposure to common odors and chemicals); stress, anxiety or depressive symptoms if present; and the area of capsaicin-induced secondary punctate hyperalgesia; the serum concentration of immunological markers (that is, IL-1β, IL-2, IL-4, IL-5, IL-6, IL-8, IL-10, IL-12, IL-13, IL-17, IL-21, IL-22, IL-23, TNFα, IFNγ); and can significantly improve quality of life.

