#### Primary outcome

##### Quick environmental exposure and sensitivity inventory

The QEESI was developed as a screening questionnaire for MCS to facilitate the recording of patient anamneses [45]. In this study, three of five original scales will be used by means of an evaluated Danish translation [46]: Symptom Severity Scale, Chemical Intolerance Scale, and Life Impact Scale. Each scale contains 10 items that produce a score ranging from 0 to 100. The QEESI Life Impact Scale is the primary outcome measure in this trial.

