#### Secondary outcomes

##### Quick environmental exposure and sensitivity inventory

The QEESI Symptom Severity and Chemical Intolerance Scales will be used to measure the severity of general symptoms and of exposure-related symptoms, respectively.

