##### Sheehan disability scale

The Sheehan Disability Scale is widely used in psychiatry, but has also been applied to many other chronic illnesses. This scale uses visuospatial, numeric and descriptive anchors to measure impaired functioning in three domains: work, social life and family life [47]. The scale generates four disability scores, one for each domain and a total score by adding up the three individual domain scores.

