##### Individual self-selected tasks

In addition to the Life Impact Scale used as the primary outcome measure, the participants will be asked to select three tasks in the areas of work, social life and family life, which are impaired by MCS at baseline. The degree of impairment associated with each task is scored on a scale from 0 to 10 with visuospatial, numeric, and descriptive anchors similar to the Sheehan Disability Scale.

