##### Noise sensitivity

To measure the participants’ sensitivity to noise, they will be asked to grade their responses to 10 different noises (for example, drone of a machine, stroke of a hammer, rustling of paper) on a 5-point Likert scale.

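### The printed success criterion rests on the primary and secondary outcomes together, which conflicts with a design that has one primary outcome and is powered on it alone

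*Protocol article*

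**What the plan says.** - **Success rule** (Statistical analyses): the criteria of success are "significantly positive changes in the intervention group compared with the control group regarding the primary and secondary outcomes". The sentence does not say whether all, some or an ordered subset of the secondary outcomes must be significant.
- **Level** (Statistical analyses): "Intention-to-treat analyses with a two-sided significance level at 0.05 will be conducted using the mixed-model repeated-measures method for continuous measures". No other level is given.
- **Primary outcome** (Primary outcome): "The QEESI Life Impact Scale is the primary outcome measure in this trial". The Hypotheses section likewise has one primary hypothesis.
- **Sample size** (Sample size): 17 per group for power 0.80 at two-sided 0.05, from a 40% fall on the Life Impact Scale, mean 61.5 and standard deviation 24.3. No power is given for any secondary outcome.
- **Secondary outcomes** (Secondary outcomes, Table 1): a long and mixed set. For example, for the Sheehan scale "The scale generates four disability scores, one for each domain and a total score"; participants "select three tasks in the areas of work, social life and family life"; and the secondary hypotheses include "the serum concentration of immunological markers", with 15 cytokines listed.

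**The concern.** The sentence that decides whether the trial has succeeded does not match the rest of the design. The hypotheses, the choice of primary measure and the sample size all treat the Life Impact Scale as the one outcome that answers the question. The success sentence adds the secondary outcomes with a plain *and*.

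Taken at its word, a trial with a clear Life Impact benefit would fail formally if, say, one cytokine did not move. It would also fail if the distress scores did not move, although the Hypotheses section expects those to fall only where such symptoms are present. The stated power would then describe a different event from the one called success. And because the sentence does not say how the secondary outcomes count, the reading could be settled after the results are known.

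**Working it through.** **1. The plan's own figure.** Expected difference: 0.40 × 61.5 = 24.6 points. Standardised: 24.6 / 24.3 = 1.012. Normal approximation: n = 2 × (1.960 + 0.842)² / 1.012² = 15.3, so 16 per group. With the exact noncentral t distribution, power is 0.791 at 16 and 0.816 at 17, so 17 is the smallest number that reaches 0.80. Adding 3 dropouts gives 20 per group, 40 in all. The plan's figure reproduces, for the primary outcome only.

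**2. How many outcomes the rule covers.** The article gives no count, so two are used.

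- By row of Table 1: 14, that is 1 primary and 13 secondary.
- By separate score: 2 QEESI + 4 Sheehan + 3 individual tasks + 1 noise + 3 SCL-92 + 1 HAM-D6 + 1 PSS-10 + 4 WHOQOL-BREF domains + 1 hyperalgesia area + 1 capsaicin pain + 15 cytokines = 36 secondary, 37 with the primary. This assumes one noise total and separate testing of each task. It includes the pain score, which has no row in Table 1.

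**3. Literal reading: all significant in the favourable direction.** The chance of meeting the rule cannot exceed the power of the primary test (0.816 at 17 per group), and equals it only if every secondary outcome is significant whenever the primary is. To show the likely fall, assume 80% power for each of K measures and a common correlation ρ between test statistics. The article gives neither. Then

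P(all) = ∫ [1 − Φ((1.960 − 2.802 − √ρ·u) / √(1 − ρ))]^K φ(u) du,

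where 2.802 = 1.960 + 0.842. At ρ = 0 this is 0.8^K.

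| ρ | K = 14 | K = 37 |
|---|---|---|
| 0 | 0.044 | 0.0003 |
| 0.3 | 0.21 | 0.08 |
| 0.5 | 0.33 | 0.20 |
| 0.7 | 0.46 | 0.36 |
| 0.9 | 0.62 | 0.57 |

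Every entry is below 0.80.

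**4. A looser reading: any favourable secondary result counts.** This drops the printed *and*, so it only shows what the gap in wording could admit. With no effect on any outcome, and counting only results in favour of PEMF (one-sided 0.025 each),

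P(at least one) = 1 − ∫ Φ((1.960 − √ρ·u) / √(1 − ρ))^K φ(u) du.

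| ρ | 13 secondary | 36 secondary |
|---|---|---|
| 0 | 0.28 | 0.60 |
| 0.5 | 0.17 | 0.28 |
| 0.7 | 0.12 | 0.18 |
| 0.9 | 0.07 | 0.09 |

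The nominal figure for one test in the favourable direction is 0.025.

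**5. Success tied to the primary outcome alone.** Type I error is 0.05 two-sided (0.025 in favour of PEMF). Power is 0.816 at 17 per group, or 0.877 if all 20 per group are analysed. This agrees with the Sample size section.

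**The case against.** The sentence may be no more than loose drafting. The article does separate a main purpose and a primary hypothesis from secondary ones, so it has a hierarchy of intent. The criterion could mean that each hypothesis is judged on its own outcome, or that the primary must succeed with support from secondary outcomes. Requiring the primary plus at least one secondary would keep type I error at or below 0.05. Rules for testing among secondary outcomes are commonly left to the analysis plan, which is not at hand. The count of 37 is a reviewer's count, and it includes both the Sheehan total and its three components.

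Much of this stands. A reader might infer that the rule must be either unreachable or grossly inflated. The article does not support that:

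- All or any are not the only two readings.
- The figure of 0.0003 needs independence, which is implausible for overlapping questionnaires filled in by the same patients, as well as an assumed 80% power on each measure.
- A reader might also infer that a null primary with one significant cytokine could be declared a success. That fails under any reading that keeps the *and*.
- Two-sided rates for at least one p < 0.05 are not the right measure either, because the rule counts only favourable changes.

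What the objection does not remove is the conflict in the printed text. None of the milder readings is stated. This is not a detail left to the analysis plan: the article prints a success rule, and that rule does not fit the design around it. The conclusion also holds with the smaller count of 14.

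**Conclusion.** The concern holds as a conflict between the stated success rule and the single-primary design. Under the literal reading, success on the Life Impact Scale is necessary but not sufficient, and the chance of success is well below the planned 0.80: at correlation 0.5 about 0.33 (14 measures) or 0.20 (37 scores), and about 0.6 at correlation 0.9. The sizes rest on assumed correlations and an assumed 80% power for each secondary outcome. The direction does not, since each added requirement can only lower the chance of success or leave it unchanged.

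The false-positive figures of about 17% to 28% at correlation 0.5 apply only if the rule were relaxed to any favourable secondary result, which departs from the text. The primary test keeps its type I error, and the sample size calculation stands for that test.

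**What to change.** Replace the success sentence with:

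> *Success is a statistically significant between-group difference in favour of PEMF on the QEESI Life Impact Scale (two-sided 0.05) at [primary time point]. Secondary outcomes are supportive and do not determine success.*

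The sponsor must name the time point, and should make the change before any unmasked results are seen. The article plans to unmask the investigators once the last participant finishes treatment. A fixed testing order or a false discovery rate adjustment for the secondary outcomes is optional and not needed to remove the conflict.

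The cost is one sentence, with no new data and no change to sample size or procedures. The downside is that secondary results could not by themselves support a claim of success.

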### Ethical considerations

The study has obtained approval from the regional ethics committee (registration number: H-1-2013-006) and the Danish Health and Medicines Authority (EUDAMED CIV-ID number 13-01-009621) and is registered with the Danish Data Protection Agency.

In previous studies, only few and mild adverse effects related to transcranial PEMF therapy have been reported. These include mild transient nausea and headache. If serious adverse events should occur, an evaluation will be carefully conducted in order to establish whether the event is related to PEMF therapy or other parts of the study. If an association between the serious adverse event and PEMF therapy is suspected, the allocation sequence for the participant concerned will be unmasked. Any adverse effect or event reported during the study will be registered and reported to the relevant authorities and in future publications.

The study will be conducted in accordance with Good Clinical Practice guidelines and will be monitored by the GCP Unit at Copenhagen University Hospital.

## Discussion

MCS is a condition that may have substantial individual and social consequences. In spite of this, an effective treatment for MCS has not yet been documented. This trial will test whether PEMF therapy can effectively ameliorate the negative effects of MCS in a randomized controlled design. The main strength of the study is that this is the first randomized, double-blind, placebo-controlled trial assessing a possible treatment for MCS. The results will show whether PEMF therapy is beneficial for MCS patients in terms of impact on patients’ lives, symptoms, psychological distress, life quality and whether an associated capsaicin-related CNS response and immunological markers are influenced by the intervention.

Some limitations of the study must be considered. Although the case criteria used in this study are generally accepted, there is no officially approved case definition for MCS and the case criteria are based on self-report because no objective clinical tests are available to confirm the condition.

Furthermore, the study will include MCS patients who experience severe functional impairments because of MCS, which means that the outcomes of the study may not be applicable to all MCS cases. However, in light of the absence of objective clinical tests, functional impairment is a clinically relevant parameter in the assessment of a possible treatment effect. Apart from the fact that a treatment with well-documented effects on MCS is absent, there is very little else to offer these patients in terms of healthcare in general. There is thus a great need for well-conducted randomized trials aimed at assessing possible treatment effects. PEMF therapy is a promising treatment, which can be targeted at the CNS, and a positive outcome of this trial will pave the way for improved healthcare and understanding of this very disabling and overlooked condition.

## Trial status

Participants are being recruited for the study.

## Abbreviations

CNS: Central nervous system; IFN: Interferon; IL: Interleukin; MCS: Multiple chemical sensitivity; PEMF: Pulsed electromagnetic fields; QEESI: Quick Environmental Exposure and Sensitivity Inventory; TNF: Tumor necrosis factor.
